# Effects of a Community Health Worker–Led Health Literacy Intervention on Lifestyle Modification Among Patients With Hypertension and Diabetes in the City of Harare, Zimbabwe: Protocol for a Cluster Randomized Controlled Trial

**DOI:** 10.2196/47512

**Published:** 2023-10-03

**Keywords:** hypertension, diabetes, community health worker, lifestyle modification, cluster randomized controlled trial, protocol, Harare, Zimbabwe, RCT, randomized controlled trial, hypertensive, blood pressure, CHW, diabetic, Africa, healthy lifestyle, health literacy

## Abstract

**Background:**

Hypertension and diabetes are among the most common noncommunicable diseases in Zimbabwe. These 2 conditions are largely prevented and controlled by lifestyle modifications, such as healthy eating habits, physical activity, and avoiding the use of tobacco and alcohol.

**Objective:**

This study aims to evaluate the effects of a community health worker (CHW)–led health literacy intervention on lifestyle modification among patients with diabetes and hypertension in the City of Harare, Zimbabwe, in terms of (1) adherence to recommended lifestyle changes, (2) blood pressure and blood glucose levels, and (3) medication adherence.

**Methods:**

This is a 6-month–long cluster randomized controlled trial, which will be conducted in primary health care clinics in the city of Harare. A total of 14 clinics will be randomly allocated into either the intervention or control group. A total of 680 (49 participants per clinic) adult patients with hypertension and diabetes will be enrolled for the trial. Participants in the intervention arm will receive a simple health literacy intervention on lifestyle modification, which will be delivered by trained CHWs, while those in the control arm will receive usual care. The intervention consists of 4 face-to-face interactive educational sessions and monthly support visits by trained CHWs and will be carried out over a period of 6 months. The primary study outcomes will be blood pressure and blood glucose levels and levels of adherence to the recommended lifestyle modifications. Other outcomes will include adherence to medication. Data management and analysis will be done using Epi Info software, and the data will be analyzed using the intention-to-treat principle.

**Results:**

Recruitment of study participants commenced on June 1, 2023, and was completed on July 30, 2023. Baseline data are being collected after participants’ recruitment, and the final data collection will be completed by January 31, 2024.

**Conclusions:**

There is an information dearth regarding the effectiveness of CHW-led interventions for the management and control of hypertension in Zimbabwe. Our study offers an opportunity to show the effectiveness of CHWs in addressing the gaps in the management of hypertension and diabetes. The findings from our study will provide crucial evidence on the effectiveness and feasibility of a simple intervention delivered by CHWs in resource-constrained areas.

**International Registered Report Identifier (IRRID):**

PRR1-10.2196/47512

## Introduction

Hypertension and diabetes are among the leading causes of morbidity, disability, and premature death worldwide. In 2019, diabetes was the direct cause of 1.5 million deaths worldwide, and 48% of all deaths due to diabetes occurred before the age of 70 years [1-3]. An estimated 1.28 billion adults aged 30-79 years worldwide have hypertension, with an estimated 46% being unaware of their condition. The prevalence of both hypertension and diabetes has been increasing more rapidly in low- and middle-income countries, compared to high-income countries. This is a cause for concern in these countries, considering their already high burden of communicable diseases [1,3].

Studies have shown links between hypertension and diabetes [4-6]. For instance, hypertension is more common in patients with diabetes, and similarly, diabetes is also more common in patients with hypertension than in the general population [4]. Previous studies have reported that hypertension occurs in 50% to 80% of patients with type 2 diabetes [5]. These two conditions are predominantly lifestyle related, as they are highly associated with risk factors like obesity, stress, excessive salt intake, physical inactivity, excessive alcohol intake, and smoking [3,6,7]. Therefore, prevention, control, and management of these two conditions involve lifestyle modifications. The recommended lifestyle changes include weight reduction, healthy eating, reducing alcohol consumption, regular physical exercise, and quitting smoking [8-10].

Lifestyle modification poses a challenge for patients with hypertension and diabetes, and several studies have demonstrated high noncompliance with the recommended lifestyle modifications worldwide [11]. Although studies have shown that nonadherence to recommended lifestyle modifications is influenced by several factors, inadequate knowledge and lack of support have constantly been highlighted as major contributing factors [12-17]. Therefore, there is a need for educational interventions to assisst patients with hypertension and diabetes in adopting the reccommended lifestyle modifications easily. In most instances, counseling about the reccommended lifestyle modification is done by physicians and nurses as part of their routine clinical care [14]. However, in resource-limited settings, where there is a shortage of health care workers, effectively counseling patients on the reccommended lifestyle modifications poses a challenge [18]. As a result, there is a need to explore other cost-effective strategies to ensure the effective counseling of patients regarding lifestyle modifications. Task-shifting to community health workers (CHWs) has been proven as one such cost-effective and sustainable approach in chronic disease prevention and control, particularly in areas with limited economic and health care resources [15,16,18].

CHWs are voluntary public health workers who are trusted members of the community they serve [17]. They play a crucial role in primary and tertiary prevention of diseases, particularly in low- and medium-income countries. According to the Alma Ata Declaration on Primary Health Care, CHWs are the cornerstone of health promotion, as they facilitate community members’ participation in health programs [19]. Overall, CHWs build individual and community capacity to manage chronic conditions by increasing health knowledge and self-sufficiency through a range of activities, such as outreach, community education, informal counseling, social support, and advocacy [20-22]. In Zimbabwe, CHWs primarily provide community-based care, but for many years, their efforts have been focused on home-based care for people living with HIV and tuberculosis, with limited focus on addressing noncommunicable diseases (NCDs) [21]. This shows the need to continuously come up with effective CHW-led interventions for the management of common NCDs.

We have developed a simple CHW health literacy intervention on lifestyle modification, and we have designed a study to evaluate the effects of the intervention among patients with hypertension and diabetes in the city of Harare, Zimbabwe. This paper describes our research design and discusses the rationale of our study. We hypothesize that the intervention will have a positive effect on (1) adherence to recommended lifestyle modifications, (2) adherence to medication, as well as (3) blood glucose and blood pressure levels.

## Methods

### Study Design

The study is a cluster randomized controlled trial, which will be conducted in the city of Harare in Zimbabwe from June 2023 to January 2024. The design, implementation, and reporting of the study are based on the recommendations from CONSORT (Consolidated Standards of Reporting Trials) statement on cluster randomized controlled trials [23]. The cluster randomized controlled trial will have a 6-month follow-up period and will consist of 1 intervention arm and 1 control arm.

### Study Setting

The study will be conducted in 14 primary health care clinics in the city of Harare; these clinics were purposefully selected from a total of 39 health facilities (12 polyclinics, 6 family health services clinics, 15 satellite clinics, and 2 infectious diseases hospitals) in the city. The 14 facilities that have been selected for the study are the ones that offer comprehensive services, including curative services, chronic pain care, maternal and child health services, HIV prevention services, and community health services. These clinics are in the high-density suburbs of the city, with each clinic serving a population of 80,000-100,000 people, the majority of whom are socioeconomically disadvantaged. The 14 health facilities will be randomly allocated into either the intervention or the control arm. Thus, each study arm will comprise 7 health facilities.

### Interventions

The intervention arm will receive the CHW-led health literacy intervention, while the control arm will receive usual care.

#### CHW-Led Health Literacy Intervention for Lifestyle Modifications

The intervention was designed by the principal investigator (PI), and its development entailed two processes, as follows: (1) conducting a scoping review of the literature on CHW-based interventions for hypertension and diabetes and (2) validating the content through consultations with 10 experts (ie, 3 health promotion officers, 2 nutritionists, 2 medical doctors, 1 Diabetes Association of Zimbabwe official, 1 pharmacist, and 1 nurse). The intervention is based on the constructs of the Health Belief Model [24], and thus, it aims to (1) convey the consequences of the patient’s poor adherence to recommended lifestyle modifications, (2) communicate to the patient the list of recommended lifestyle modifications and highlight the benefits, (3) provide assistance in identifying and reducing barriers to adopt the recommended lifestyle modifications, and (4) develop cues to action for the patient.

This intervention consists of face-to-face educational sessions and support visits to patients and will be delivered by trained CHWs. A total of 4 educational sessions will be conducted at either the patient’s home or the primary care clinic, through which the patient is routinely monitored. The first session will be held at the clinic on the day of recruitment. The second and the third sessions will be held at either the clinic or the patient’s home, as preferred by the patient. The fourth session will be a home visit, where the CHW will visit the patient in their home to provide support and follow-up. After the fourth educational session, the CHWs will continue to make monthly home visits to the patient.

In terms of content, in the first session, the CHW will educate the patient on the recommended lifestyle modifications and the consequences of nonadherence. In the second session, focus will be on the patient’s barriers to adopting recommended lifestyle modifications and ways to overcome them. At the end of this session, patients are expected to write down their own plan for lifestyle modifications on a card, which they will then place in a visible location in their home. This will serve as a cue to action. The second session will be highly interactive, compared to the first session. The third and fourth sessions will be supportive and evaluation sessions during which the CHW assesses whether the patient has been following the action plan established in the second session. In the fourth session, which will be conducted at home, available family members will be involved to support the patient, and this will serve as another cue to action for the patient and will also help to build the patient’s self-efficacy. Any deviations from the plan will be discussed and ways to correct will be explored. The monthly home visits conducted after the fourth educational session will serve as support visits, where the CHW will continue to reinforce the importance of adhering to lifestyle modifications.

In terms of timing, the first session will be conducted on the day of recruitment, and the second session will be scheduled a week after the first session. The third session will be conducted 2 weeks after the second session, and the fourth session will also be conducted 2 weeks after the third session. A month after the fourth session, the patients will receive monthly home visits at a date and time convenient for them. Each educational session will last 45-60 minutes, while the monthly support visits will last 10-15 minutes.

To ensure that the intervention adheres to the protocol and maintains study fidelity, the CHWs who will deliver educational sessions will undergo a 1-day training; this training will be conducted by the PI, 1 nurse, and 1 health promotion officer from the city of Harare. The CHWs will be given notes on the recommended lifestyle modifications, to which they will refer when conducting educational sessions. All the CHWs participating in the study have been working as CHWs for periods ranging from 5 to 30 years, and upon their initial recruitment as CHWs, they underwent an 8-week training program. They will also receive refresher trainings as needed, in accordance with the guidelines for CHWs in Zimbabwe [21,25].

#### Usual Care

The usual care for patients with diabetes and hypertension in the city of Harare involves patients coming to the clinic for monthly reviews and medication collection. Patients also receive counseling on medication adherence and recommended lifestyle modifications, particularly on the day when they are diagnosed and start their medication. Although there is no formalized CHW intervention, CHWs are involved in the continuum of care when patients fail to report for their monthly reviews for 3 consecutive months. Additionally, patients may seek consultation with CHWs in their communities, as needed. Table 1 summarizes the interventions that will be implemented in this study.

**Table 1 table1:** Summary of study interventions.

Component	Control arm (usual care)	Intervention arm (community health worker–led health literacy intervention)
Main components	Health education session on the importance of adhering to medication and lifestyle modifications on the day medication is initiated by a nurse or doctor and monthly drug pickups at local health facilities	Usual care and 4 interactive educational sessions and monthly home visits by community health workers
Theoretical background of educational sessions	None	Health Belief Model [24]
Role of community health workers	Follow-up when the patient misses clinic appointments for 3 consecutive months	Continuous support in the management and control of diabetes and hypertension

#### Randomization

All 14 targeted health facilities will be randomly allocated to either the intervention or the control arm. Each arm will consist of 7 clinics. The randomization process will be conducted by an official from the city of Harare, from the City Health Department, who will not be part of the study staff. The randomization process will be done using the simple randomization technique, based on computer-generated random numbers. To reduce bias and improve study fidelity, group allocation will be concealed to the data collectors until the completion of baseline data collection.

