#### Recruitment of Participants

Participants will be recruited by trained research assistants every day of the 1-week recruitment period. The recruitment process will be done concurrently at control and intervention sites. Baseline data will be collected on the day of the recruitment, and research assistants will not be aware of group allocations during the recruitment and the baseline data collection periods.

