#### Outcome Measures

The outcome evaluation for this study will be based on data collected both at baseline and during the postintervention follow-up (after 6 months). Data collection tools will be identical for data collection at both periods and include information on patient’s demographics, disease history, lifestyle behaviors, medication use, primary use of health care services, and hospitalizations. Height, weight, waist circumference, glycosylated blood glucose levels, and blood pressure will also be measured.

The primary study outcomes will be blood pressure and blood glucose levels as well as levels of adherence to recommended lifestyle modifications. Other outcomes will include changes in medication adherence and additional health-related outcomes, such as frequency of hospitalization or the occurrence of complications.

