#### Assessment of Primary and Secondary Outcomes

A consolidated interviewer-administered questioner comprising of all measures (as detailed in Multimedia Appendix 1) will be used to collect data. The interviewer-administered questionnaire consists of 5 sections, as follows: section A (sociodemographic characteristics), section B (details of the patient’s condition), section C (blood pressure, BMI, and glycosylated hemoglobin [HBA_1c_] measurements), section D (adherence to lifestyle modifications), and section E (adherence to medication).

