### Strengths and Limitations

The strengths of our study include CHWs who are already integrated in the Zimbabwean primary health care system. The CHWs have prior experience in disseminating health education on various health topics, particularly prevention of diarrheal diseases and malaria, which are prevalent in the country. Additionally, the CHWs are routinely involved in follow-ups with patients who have hypertension and diabetes, ensuring they do not miss monthly checkups. Therefore, if successful, our intervention will modify and strengthen community-based management of hypertension and diabetes. Unlike most of the CHW-based interventions being implemented in other low- and middle-income countries, our intervention is based on a tested and tried health behavior model, the Health Belief Model [24]. Therefore, we envisage that the intended behavior change in the adoption of recommended lifestyles will be successful. Moreover, our intervention will be innovatively addressing some of the most challenging barriers to the management of chronic NCDs, such as human resources. Hence, if successful, this intervention can be potentially scaled up to the entire nation.

Nonetheless, there are weaknesses in our study, mainly emanating from the cluster randomized controlled trial design. First, our study does not involve blinding of study participants. Lack of blinding is one of the weaknesses inherent in cluster randomized controlled trials that include behavioral interventions. However, to reduce bias associated with lack of blinding, there will be partial blinding of data collectors during the collection of baseline data. The data collectors will not know the arm to which each clinic will belong. In addition, there is a possibility of information sharing among participants in the intervention and control group, since the suburbs in Harare are within close proximities. To limit the sharing of information, participants in the intervention group will receive a detailed explanation of the study’s importance from the PI. There is also a possibility of social desirability bias in assessing lifestyle modifications. Participants may report what they perceive as the desired behavior rather than their actual behavior. However, the study will assess overall changes in blood glucose and hypertension levels as well as BMI, which are more objective outcome measures.

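### Data collectors are masked only through baseline, leaving the 6-month self-reported lifestyle outcome and blood pressure without masked assessment

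*Protocol article*

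**What the plan says.** Three sections of the protocol article describe masking of data collectors, and all stop at baseline. Randomization states that "group allocation will be concealed to the data collectors until the completion of baseline data collection". Recruitment of Participants states that "research assistants will not be aware of group allocations during the recruitment and the baseline data collection periods". Strengths and Limitations first concedes that "our study does not involve blinding of study participants" and then offers as mitigation that "there will be partial blinding of data collectors during the collection of baseline data".

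Outcome Measures bases the evaluation on baseline and 6-month data and states: "The primary study outcomes will be blood pressure and blood glucose levels as well as levels of adherence to recommended lifestyle modifications". Assessment of Primary and Secondary Outcomes describes the instrument as "A consolidated interviewer-administered questioner comprising of all measures". Its section C holds blood pressure, BMI and HbA1c, section D lifestyle adherence, and section E medication adherence. Data Collection and Management has the data entered on the research assistants' phones and names no separate follow-up team.

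On the start of the intervention, the section describing the CHW-led intervention states: "The first session will be held at the clinic on the day of recruitment". Recruitment of Participants puts baseline collection on that same day, with recruiting on every day of a 1-week period. The Results section gives recruitment dates of June 1 to July 30, 2023.

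**The concern.** Masking of assessors matters most when the outcome is measured after the arms have diverged. Here concealment has a stated end point, and it falls before that measurement. An interviewer who knows a clinic's arm can influence how self-report questions are put and how answers are recorded. To a lesser degree, such knowledge can also affect how blood pressure is taken and written down. Patients are unblinded, and the article already accepts that they may report the behaviour they think is wanted. An unmasked interviewer could add to that.

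The second issue is at entry. Clinics are allocated as whole clusters and patients are enrolled there over successive days. If recruiters learn a clinic's arm partway through, who is approached or enrolled could come to differ between arms.

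**Working it through.** **Step 1: masking stated at each stage.**

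| Stage | What is collected | Masking of collectors stated |
|---|---|---|
| Recruitment and baseline | Full questionnaire and measurements | Yes (Randomization; Recruitment of Participants; Strengths and Limitations) |
| 6 months | The same tools again | None in any section |

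That follow-up staff may know the arm is an inference from the stated end point of concealment. It is the plain reading, and nothing in the article contradicts it.

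**Step 2: which outcomes are exposed.**
- Lifestyle adherence (primary): self-reported to an interviewer. High.
- Medication adherence (secondary): in the same questionnaire. High.
- Blood pressure (primary): taken at the visit, with no device or procedure described. Moderate.
- HbA1c (primary): a biochemical value. Low.
- Hospitalization and complications: taken from clinic records (Other Health Outcomes). Low.

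**Step 3: what a given bias would do.** The article gives no figure for the bias, so this shows sensitivity only. Inputs from the article are 7 clinics per arm, 49 patients per clinic and 20% loss, which leaves 49 × 0.8 ≈ 39 per clinic. Assumed inputs are a continuous outcome with SD 1, no true effect, a two-sided 5% test that allows for clustering (normal approximation), intracluster correlation (ICC) 0.01 to 0.09, and a differential measurement bias b of 0.1 to 0.3 SD.

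SE = √[2(1 + 38 × ICC)/(7 × 39)]

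False-positive rate = 1 − Φ(1.96 − b/SE) + Φ(−1.96 − b/SE)

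Example: with ICC 0.05, SE = √(2 × 2.9/273) = 0.146. With b = 0.1, b/SE = 0.69 and the rate is 10.5%.

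| ICC | SE | b = 0.1 | b = 0.2 | b = 0.3 |
|---|---|---|---|---|
| 0.01 | 0.101 | 16.9% | 51.2% | 84.7% |
| 0.05 | 0.146 | 10.5% | 27.9% | 53.9% |
| 0.09 | 0.180 | 8.6% | 19.9% | 38.5% |

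Masking at baseline does nothing to change these figures.

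**Step 4: session 1 against recruiter masking.** Assume even accrual at a clinic over D days. The share of its patients recruited after the first day, when same-day CHW sessions may already have begun there, is 1 − 1/D.
- 1-week period: 1 − 1/7 = 86%.
- June 1 to July 30, if every clinic recruited daily throughout (60 days): 1 − 1/60 = 98%.

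The higher figure falls back to 86% if clinics recruited for one week each at different times, which the article does not say. The shares show how many patients were enrolled when the arm could have become visible, not how many were enrolled by someone who knew it.

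**The case against.** The strongest reply is that this is an acknowledged choice. Strengths and Limitations lists lack of blinding as a weakness, calls the masking partial, and points to blood glucose, blood pressure and BMI as more objective measures. That is fair as disclosure. But the objective-measures answer is directed at social desirability in patients. It protects neither the self-reported primary outcome from an interviewer who knows the arm nor blood pressure readings taken by such a person.

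Several stronger readings are tempting, and the article does not support them:
- That every 6-month outcome is compromised. HbA1c leaves little room for observer influence, and two outcomes come from clinic records.
- That collectors are told the allocation. The article only ends the concealment.
- That blood pressure is read manually, or that interviewers prompt answers. No device is described, and the questionnaire appendix is not shown.
- That baseline masking is impossible. A patient's baseline could precede session 1, the session could take place out of recruiters' sight, and CHWs already have a role in usual care, so seeing one need not reveal the arm.
- That the bias can be expressed as a fraction of the design effect. Sample Size gives an effect size of 0.5 without tying it to an outcome.

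Patients may also disclose their arm, and colleagues may talk, so masked follow-up would be imperfect. That limits the gain but does not remove the reason to try.

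**Conclusion.** The point stands for the 6-month assessment. Three sections end data-collector masking at baseline and none provides it at follow-up, where two of the three primary outcome domains are open to observer influence. This is a stated rule that leaves avoidable bias, and disclosing it does not cure it.

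The size and direction of the bias cannot be estimated from the article. The sensitivity figures rest on assumed bias and ICC values for a continuous outcome, whereas Table 2 classes most lifestyle items as adherent or not. They show only that a modest shared bias would matter and that analysis could not separate it from an effect.

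The timing of session 1 against recruiter masking is a practical tension that needs explanation, not a strict contradiction, and is held with less confidence. It weighs more if recruitment ran for two months and not one week.

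**What to change.** **Follow-up.** Change the Randomization section so that allocation stays concealed from data collectors until 6-month data collection is complete. Wording alone would be nominal, so support it as follows:
- assign existing research assistants to follow up only at clinics where they did not recruit, without telling them the arm;
- keep CHWs out of the assessment;
- take blood pressure and HbA1c before the questionnaire;
- record each assessor's guess of arm.

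Align Recruitment of Participants and Strengths and Limitations with this. When the article appeared in October 2023, follow-up was still due in January 2024, so the change was then possible. If follow-up has since been done as written, report who collected the data and whether they knew the arm, and interpret self-report and blood pressure accordingly.

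**Recruitment.** Recruitment has closed, so this part is explanation and reporting. Reconcile the session 1 timing with the two statements on recruiter masking, and the 1-week period with the June 1 to July 30 dates. State how recruiters stayed unaware of allocation, and report baseline comparability of those enrolled.

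**Cost.** Rota planning and some travel, with no extra staff. Some unmasking by patients or colleagues will remain, and masked interviewers do not remove patients' own reporting bias.
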